### Ethics

This study is conducted in accordance with the principles of the Declaration of Helsinki and 'good clinical practice' guidelines. The independent medical ethics committees of the participating centers have approved the study protocol. Prior to randomization, written informed consent will need to be obtained from all patients.

## Surgical Technique

### Pre-operative regimen

Pre-operative preparation has the aim of keeping patients physically and mentally as optimal as possible during the whole period of pre-operative period. Complete information about the diagnostic phase, randomization, neoadjuvant therapy and surgical intervention is very important here. Coordination of this preparation period is undertaken by a research nurse, the study-coordinator and the participating surgeons.

All patients will have regular consultations by a dietician during the whole pre-operative path. Supplemental nutritional feeding can be initiated and if necessary a thin nasogastric tube can be placed for feeding purposes. Also, all patients will be consulted by a physiotherapist for exercises with emphasis on respiratory improvement. If necessary, a psychological consultation will be arranged.

### Neoadjuvant therapy

All patients included will pre-operatively receive neoadjuvant therapy: chemoradiotherapy or chemotherapy alone according to local protocol. Each center will treat patients, either in category open operation or MIE, in the same way.

### Esophageal resection

The open operation as well MIOE operation consists of a two-field esophageal resection with gastric tube formation followed by cervical or thoracic anastomosis.

For patients undergoing a thoracotomy, a high epidural catheter and a double tube are placed for selective intubation.

### Traditional transthoracic esophagectomy

In the open group a three-stage procedure is followed. After selective intubation to block the right lung, the patient is placed in a left lateral decubitus position. The first stage is started with a right posterolateral thoracotomy. The esophagus and its overlying mediastinal pleura is mobilized with mediastinal and carina lymphadenectomy. For the second stage, the patient is turned to a supine position. Through a supra-umbilical laparotomy the stomach is mobilized with special care of the gastro-epiploic vessels and a lymphadenectomy of the celiac trunk is performed. The dissection finalizes at the hiatus with anterior extension and careful dissection of the gastro-esophageal junction along the planes. For the last stage a cervical incision is made and the esophagus dissected free. Retrieval of the specimen through the laparotomy wound is performed and a gastric conduit created. No pyloroplasty is usually performed. A jejunostomy catheter is placed for feeding purposes. A gastric tube-esophageal anastomosis is then established in an end-to-side fashion.

If an thoracic anastomosis is made, the first phase of it commences with an abdominal approach involving the patient in supine position. The second phase (thoracic) is performed with the patient in a left decubitus position. The retrieval of the specimen will be achieved through the thoracotomy wound. The anastomosis will be made high in the thorax, proximal at the level of the divided vena azygos.

### Minimally invasive transthoracic esophagectomy

The MIE also has a three-stage procedure. The difference from the procedure of the open operation is that there is no need for selective intubation with the exception of patients in whom an thoracic anastomosis is planned (a Fogarty balloon catheter is placed under bronchoscopy view in the right primary bronchus and inflated only during the anastomosis phase). After anesthesia, the patient is turned to a prone position. Four trocars are placed along the medial edge of the scapula. Modest insufflation using CO2 will raise the intrathoracic pressure between 6 and 8 mmHg. Radical esophagectomy is performed along the pericard sac, pulmonal veins, right bronchus, aorta resecting the esophagus with the mediastinal pleura and lymphadenectomy (peri-esophageal, lower posterior mediastinal, carina and right paratracheal). After completion of this phase the thorax is drained and the trocar sites are closed.

The patient is then placed in a supine position. After introduction of four trocars the mobilization of the stomach is performed similar to the traditional procedure (with paracardiac left and right, lesser and greater curvature and celiac trunc lymphadenectomy). After dissection of the esophagus at cervical level, the specimen is retrieved through a well protected trans-umbilical mini-laparotomy (6-8 cm). The esophageal-proximal stomach resection is performed extra-corporeally and a small gastric conduit (3-4-cm) created, then conducted to the cervical wound and there anastomosed. A jejunostomy catheter is placed.

If a thoracic anastomosis is made (two phase procedure), the first phase commences with a laparoscopy involving the patient in supine position. The only difference with the three stage MIE (abovementioned) is the laparoscopic creation of the gastric tube and hiatal dissection. A jejunostomy catheter is placed. The second phase (thoracic) is performed with the patient in prone decubitus position. The esophagus is dissected free up to the distal trachea, the azygos vein is divided and lymphadenectomy performed. After division of the esophagus, a purse string is placed at the proximal esophagus. A posterior mini-thoracotomy (6 cm) is performed, the lung is blocked, and a 25 circular stapler anvil placed in the proximal esophagus. The specimen is retrieved, resected and through it the circular stapler is placed and an end-to-side anastomosis performed. The rest of the loop is resected by an endoscopic stapler and the thoracic cavity drained.

### Post-operative management

Patients in both groups will receive similar post-operative treatment. All patients will after surgery be admitted intubated at the intensive care unit (ICU). After stabilization and detubation, the patient will if indicated be admitted to the general surgical ward or to the medium care unit (MCU). In the first days after surgery analgesics are administered by the epidural route. In the event of epidural failure, post-operative pain will be treated intravenously by a 'patient controlled analgesia' (PCA); when necessary through a pump with morphine. Patients will be instructed about the PCA pump by an anesthesiologist and morphine doses will be noted. Patients will have a nasogastric tube in-situ for at least 5 days as some gastric conduit distension is expected. All patients will receive postoperative physiotherapy for breathing-exercises the day after surgery. To regain early mobilization, starting day 1, patients are encouraged to sit out of bed in the general surgical ward. Enteral feeding is commenced day 1 after operation through the jejunostomy and increased to optimal feeding at day 3. At day 5, after gastrographine swallow X ray, the nasogastric tube is retired and started with liquids. Normal diet can be progressively resumed while jejunostomy feeding is decreased. Patients will be discharged when they are able to eat normal food, can walk and are comfortable with oral analgesia. Delay to "social" reasons will be noted. Completion of the feeding over the jejunostomy may be continued after discharge. Patient follow-ups are carried out at the outpatient clinic at 6 weeks, 3 months, 6 months and 1 year after discharge. During these visits, the quality of life questionnaires (SF-36 and EORTC QLQ-OES18) will be completed. The regular follow-up will continue up to 5 years after surgery.

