The three main surgical approaches utilized worldwide for intrathoracic esophageal cancer are the following: (1) the three stage transthoracic resection (i.e. right postero-lateral thoracotomy, laparotomy and cervicotomy) with a cervical anastomosis; (2) the two stage transthoracic resection (i.e. laparotomy, and right postero-lateral thoracotomy, including the Ivor Lewis approach with an intrathoracic anastomosis); and (3) the two stage transhiatal resection (i.e. laparotomy and cervicotomy with cervical anastomosis) [4]. Transhiatal esophagectomy according to Orringer is generally performed for gastro-esophageal junction cancers [5]. Nevertheless, cancer of the lower esophagus metastasized, according to the Tumor-Node-Metastasis classification, in more than 45% to the lymph nodes in mediastinum and carina. Therefore patients with reasonable general condition are increasingly surgically approached transthoracically. In the randomized study by Hulscher et al. and long term follow-up, comparing the transhiatal and transthoracic esophageal resection, an important trend of better survival has been observed in the transthoracically approached patients [6,7]. This transthoracic procedure is associated with a high morbidity and mortality rate of approximately 50-70% and 5% respectively [6]. Moreover, the extensive nature of this open approach has a significant negative impact on the quality of life of these patients and is associated with a long in-hospital recovery.

Minimally invasive esophageal (MIE) resection for cancer avoiding the thoracotomy and laparotomy can reduce the amount of trauma of the required surgery with the same oncological value. This will imply a reduction of the post-operative morbidity, a shortening of the recovery time and an increase of quality of life. Evidence of the short term benefits of minimally invasive surgery over open procedures with similar oncological outcome is accumulating. Less perioperative complications, shorter hospital stay and faster post-operative recovery appear to be the main advantages. MIE involves a right thoracoscopy and laparoscopy, either with a cervical or intrathoracic anastomosis. The thoracic phase of this procedure can be performed through a lateral right thoracic approach with a right lung block by selective intubation or in prone position without selective lung block. This prone approach, with partial lung collapse, will result in lower percentage of pulmonary complications [8,9].

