## Methods

### Study objectives

The TIME trial is prospective, multi-center, randomized study comparing traditional transthoracic esophageal resection with minimally invasive resection for esophageal cancer. Patients with resectable intrathoracic esophageal cancer are randomized for either (a) minimally invasive transthoracic esophageal resection in prone position or (b) traditional open transthoracic esophageal resection. Our hypothesis is that patients undergoing a minimally invasive esophagectomy have fewer morbidity, a shorter duration of the intensive care unit (ICU) admission and a better quality of life than following the traditional approach.

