### Data collection and statistics

Data are transcribed via datasheets on paper and sent to the VUmc by surface mail. Data are collected daily until the day of discharge. The quality of life questionnaires (SF-36 and EORTC-OES18) are completed by the patient starting preoperatively and post-operatively at 6 weeks, 3 months, 6 months, and at 1 year. There will be regular contact between the study-coordinators and the participating centers. One research fellow will monitor the data of all included patients. Using a SPSS database containing all required parameters, data analysis will be performed in accordance with the intention-to-treat principle, additional per-protocol analysis will also be performed. Groups are, where appropriate, compared using an Independent Samples T-test, otherwise a Wilcoxon test, or Chi-square test. Pain scores will be analyzed using repeated measures analysis.

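### The same quality-of-life questionnaires are timed from the operation in one section and from discharge in another; a discharge clock would depend on arm, though the likely bias is small

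*Protocol article*

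**What the plan says.** Two sections of the protocol article schedule the same questionnaires.

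- **Data collection and statistics:** the SF-36 and the OES18 are "completed by the patient starting preoperatively and post-operatively at 6 weeks, 3 months, 6 months, and at 1 year".
- **Post-operative management:** "Patient follow-ups are carried out at the outpatient clinic at 6 weeks, 3 months, 6 months and 1 year after discharge". The next sentence ties the instruments to those visits: "During these visits, the quality of life questionnaires (SF-36 and EORTC QLQ-OES18) will be completed".

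The paragraph on post-operative management then changes anchor for long-term follow-up: "The regular follow-up will continue up to 5 years after surgery".

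Three other statements bear on the point. Discharge is set by recovery: "Patients will be discharged when they are able to eat normal food, can walk and are comfortable with oral analgesia". Social delays to discharge are also foreseen and are to be noted. The Background says of minimally invasive surgery: "Less perioperative complications, shorter hospital stay and faster post-operative recovery appear to be the main advantages". Study objectives makes quality of life part of the hypothesis, expecting "a better quality of life than following the traditional approach" in the MIE arm; Endpoints lists it among the secondary outcomes.

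**The concern.** The four nominal times are identical in the two sections but the starting point is not, and no sentence says which governs. A reader could follow either.

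The choice matters because discharge happens after randomisation and is itself something the treatment is expected to change. Length of hospital stay is a listed outcome, and the protocol expects it to be shorter with MIE. On a discharge clock, a patient who stays longer has had more days since the operation at each nominal visit. If open-arm patients stay longer and quality of life is still rising, the open arm is measured at a later point on its recovery curve. The two arms are then not compared at the same time since surgery, and the shift works against the quality-of-life benefit that the trial hypothesises.

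**Working it through.** **Plan's own figures.** The article gives no sample size, power or expected difference for quality of life, so there is no quality-of-life figure to reproduce. The sample size for the primary endpoint reproduces: with 57% against 29%, two-sided alpha 0.05, power 0.80 and pooled variance, n = [1.960·√(2·0.43·0.57) + 0.842·√(0.57·0.43 + 0.29·0.71)]² / 0.28² ≈ 47.9, so 48 per arm, and 48/0.80 = 60. It does not depend on the questionnaire schedule.

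**Step 1: the two clocks.** Let t be the nominal visit time and L the length of stay after surgery, both in days.

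- Operation clock: day of assessment after surgery = t.
- Discharge clock: day of assessment after surgery = t + L.

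The difference between arms in time since surgery is 0 on the operation clock. On the discharge clock it equals the difference in stay, d, at every visit.

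**Step 2: the value of d.** Total hospital stay by arm is not in the article. The Discussion gives only median ICU stays, 1 day in two minimally invasive series and 6 days in an open series, a gap of 5 days between separate external studies. I therefore take d = 2, 5 and 10 days as an assumed range.

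**Step 3: shift as a share of nominal time, d/t** (t = 42, 91, 182, 365 days).

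| Assumed d | 6 weeks | 3 months | 6 months | 1 year |
|---|---|---|---|---|
| 2 days | 4.8% | 2.2% | 1.1% | 0.5% |
| 5 days | 11.9% | 5.5% | 2.7% | 1.4% |
| 10 days | 23.8% | 11.0% | 5.5% | 2.7% |

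**Step 4: from calendar shift to score.** A shift in days is not yet a bias in quality of life. To see the order of size, assume a deficit of 1 SD at surgery that halves every h days, the same in both arms. The spurious difference in favour of the longer-staying arm is

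0.5^((t + L_MIE)/h) − 0.5^((t + L_open)/h).

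Example with h = 30, stays of 20 (open) and 10 (MIE) days, t = 42: 0.5^(52/30) − 0.5^(62/30) = 0.301 − 0.239 = 0.062 SD.

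For h = 30, 60 or 90 days and stays (open against MIE) of 14 against 12, 14 against 9 or 20 against 10 days, the ranges are:

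- 6 weeks: 0.010 to 0.062 SD
- 3 months: 0.004 to 0.034 SD
- 6 months: at most 0.017 SD
- 1 year: at most 0.004 SD

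**Step 5: scale.** The difference detectable with 80% power at two-sided 0.05 is (1.960 + 0.842)·√(2/n), which is 0.57 SD for n = 48 and 0.51 SD for n = 60 per arm. The largest shift above is 0.062/0.51 ≈ 12% of that.

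**The case against.** **The wording may be loose rather than contradictory.** The data-collection section never says in so many words that the count starts at surgery. Its term stands opposite the preoperative questionnaire and could be a label for the visits defined later. The article is also condensed, and a fuller protocol may fix the time zero. This has some force, but timing from the operation is the ordinary reading. The later section moves from discharge to surgery as anchor within a few sentences, which makes it hard to treat the two as synonyms. The article itself states both schedules.

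**A reader might infer that the quality-of-life comparison is biased outright.** The documents do not support that. Three things must hold: the discharge clock is actually used, total stay differs between arms, and quality of life is still improving at the visit. The protocol expects the second without quantifying it, and gives no data on the third.

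**A reader might also take the ICU medians of 1 and 6 days as the between-arm difference in stay.** They come from separate series, not randomised arms, and are not total hospital stay. Nor should a contrast between two hypothetical patients, such as day 42 + 30 = 72 against day 42 + 10 = 52, be read as a difference between arms.

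**The consequence is limited.** If open patients stay longer, the shift attenuates an MIE advantage and does not create one. The primary endpoint is fixed at two weeks after the operation and is untouched. Randomisation is stratified by centre, so if centres follow different sections, each centre's clock still applies to both its arms. That limits the harm from differing practice but does not remove the shift at a centre that counts from discharge.

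**Conclusion.** The inconsistency stands: the same questionnaires at the same nominal times have two time zeros, and the text does not reconcile them. It also stands that a discharge clock depends on recovery and, by the protocol's own expectation, on arm. Any bias from it is conditional, and its direction is towards no difference if the open arm stays longer.

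Its size cannot be derived from the documents. For an assumed difference in stay of 2 to 10 days the shift is 5 to 24% of 42 days at the first visit and under 3% at one year. Under the assumed recovery curves this is about 0.01 to 0.06 SD at 6 weeks and negligible at one year. The bias is thus probably small, largest at 6 weeks, and limited to a secondary endpoint that nevertheless appears in the stated hypothesis. It merits correction because it is avoidable and because the date on which a questionnaire was completed cannot be changed afterwards.

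**What to change.** Reconcile the two sections by timing the questionnaires from the date of surgery in both, at 6 weeks and 3, 6 and 12 months. Record the actual completion date of every questionnaire, so that time since surgery is known whatever happened in practice. Where the clinic visit does not coincide with the due date, have the questionnaire completed by mail.

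The change concerns the questionnaires only and needs no extra visits and no change to the clinic schedule. The cost is a wording change, one recorded date per form, and mailing. The mailing should not be called occasional: if clinic visits remain timed from discharge, even a 10-day stay puts the first visit at day 42 + 10 = 52, so mailing may be routine in both arms. The sample size and the primary analysis do not change.

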## Discussion

Surgery on cancer of the esophagus is considered to be one of the most extensive and traumatic oncological surgical procedures. Open resection not only involves a long operation time and large incisions but also necessitates post-operative care in the intensive care unit, a long in-hospital recovery with decreased quality of life and carries a significant risk of morbidity and death.

MIE can reduce the post-operative morbidity, in particular the respiratory complications which are most encountered. Different landmark studies have reported significantly low pulmonary complications rates using the minimally invasive transthoracic approach. Palanivelu et al. report in their minimally invasive series of 130 patients in prone-position, 2.3% pulmonary complications [9] whereas Luketich et al. report in their series of 222 patients in left lateral decubitus MIE, 18% pulmonary complications [13]. Other authors report a similar incidence in pulmonary complications with probably a slight advantage for the thoracoscopic resection in prone position, being in the experience of the VUmc around 25%. In contrast, Hulscher et al. observed 57% pulmonary complications in patients undergoing the traditional three-stage transthoracic esophagectomy [6]. Furthermore, median length of ICU stay was 1 day in the series of Palanivelu and Luketich whereas in the traditional series of Hulscher the ICU stay was 6 days. Oncologically, the type of resected specimen and lymph nodes are comparable with the open series and disease-free and overall survival reported for MIE and traditional resection are quite comparable. These aforementioned landmark studies favor minimally invasive esophagectomy in terms of pulmonary complications and recovery.

Despite the advantages of the procedure, still only a small percentage of all esophageal resections for cancer are performed minimally invasive. Although, important MIE series have demonstrated feasibility and important short term advantages, yet to date the beneficiary effects of minimally invasive esophagectomy have not been proven by a randomized trial [10]. Therefore, a randomized comparison between traditional esophagectomy and minimally invasive esophagectomy is necessary. This randomized trial can provide further evidence supporting the minimally invasive and cost-effective approach for esophageal cancer.

## Abbreviations

VAS-pain score: Visual Analogue Scale Pain score
